## Abstract

**Background:**

Dysmenorrhea is a common menstrual complaint among adolescent girls and women of reproductive age. The treatment of dysmenorrhea is typically selected from multidisciplinary options, including complementary and alternative medicine such as acupuncture and moxibustion. However, there are few published randomized controlled trials concerning moxibustion treatment for dysmenorrhea. This trial aims to investigate the efficacy and safety of moxibustion for primary dysmenorrhea, and to identify the optimal time of moxibustion treatment for primary dysmenorrhea.

**Methods/Design:**

This protocol is for a randomized controlled trial in which the assessor and statistician will be blinded. A total of 222 eligible patients with dysmenorrhea will be randomly assigned to three groups in a 1:1:1 ratio as treatment group A (treated before menstruation onset), treatment group B (treated at the onset of menstruation), or control group C (waiting list group). The participants assigned to the treatment groups will receive suspended moxibustion treatment at *Sanyinjiao* (SP6) and *Guanyuan* (CV4), while the waiting list group will not receive moxibustion treatment until the completion of the study. The trial period will consist of three baseline menstrual cycles, three menstrual cycles of treatment, and three menstrual cycles in the follow-up period. The primary outcome will be measured by changes in the Cox Menstrual Symptom Scale and the secondary outcomes will be measured using the Visual Analogue Scale, Cox Retrospective Symptom Scale, diary entries, the Self-rating Depression Scale, and the Self-rating Anxiety Scale. The safety of moxibustion will be assessed at every visit.

**Discussion:**

This trial aims to assess the effectiveness and safety of moxibustion for primary dysmenorrhea, as well as to determine whether the optimal time of treatment for primary dysmenorrhea in clinical practice is before or after the onset of menstrual pain.

**Trial registration:**

Chinese Clinical Trial Register: ChiCTR-TRC-14004627, registered on 9 May 2014.

## Background

Dysmenorrhea is a common menstrual complaint among adolescent girls and women of reproductive age [1]. It usually consists of two subcategories: primary and secondary dysmenorrhea. The focus of this paper is primary dysmenorrhea (PD), which is defined as painful menses in women with normal pelvic anatomy. Studies using different measurements have reported the prevalence of PD as between 20 and 90% of adolescent girls [2]. An Australian study found the prevalence of dysmenorrhea varied between 16 and 91%, with symptoms becoming severely painful in 2 to 29% of the women studied [3].

Dysmenorrhea has a significant impact on women’s lives and represents a substantial public health burden [4-6]. Several studies have shown that female individuals with dysmenorrhea report that it affects their academic performance and social and sporting activities, which is a distressing finding given the availability of effective medications [7,8]. Nonsteroidal anti-inflammatory drugs are widely used as first-line therapy for women with dysmenorrhea [9,10]. However, in some women the side effects may not be well tolerated or the pain relief provided may be inadequate. Therefore, a large number of patients with PD are turning to complementary and alternative medicine such as acupuncture and moxibustion [11].

Moxibustion is widely used in Asian countries as a part of Traditional Chinese Medicine (TCM). It is a thermal treatment that involves placing ignited material (usually *Artemisia vulgaris*) near acupuncture points to cause a warm and painless sensation [12]. Moxibustion is used to regulate the meridians and visceral organs of the human body [13]. Suspended moxibustion is commonly used, which refers to the application of a burning moxa stick over the acupuncture points from a distance. In TCM, dysmenorrhea is etiologically caused by the stagnated blood or *Qi* circulation in the uterus. The pathological factors are mostly dampness, blood stasis, and *Qi* obstructions. Moxibustion as a therapy features on the effect of heat and *Artemisia argyi*, and thus can improve blood circulation in the uterus and its surrounding veins, and also help to absorb local pathological discharges in patients with PD. It is considered effective in resolving blood stagnation, *Qi* stagnation, and discomposing cold-damp coagulation, leading to an improved health state [14,15]. Clinical trials and systematic reviews have evaluated the effect of moxibustion for conditions including dysmenorrhea [16], breech presentation [17], ulcerative colitis [18], stroke [19], menopausal hot flashes [20], and constipation [21].

Since ancient times, TCM has prescribed acupuncture and moxibustion to treat dysmenorrhea. Acupuncture stimulation, which involves thrusting or twisting needles, results in various biochemical reactions that can have effects throughout the body; moxibustion uses heat stimulation at various temperatures, from mild skin warmth to tissue damage caused by burning. This heat stimulation can yield inflammatory responses and induce vasodilation by releasing mediators such as histamine and substance P around the site of moxibustion therapy [22,23]. According to TCM, the treatment of PD in clinical practice is usually started before menstruation. Several studies have used different time sequences of acupressure in dysmenorrhea to seek evidence-based medical proof regarding the appropriate point selection and timing of intervention in PD [24]. Unfortunately, clinical trials regarding the optimal time of moxibustion treatment intervention are lacking.

This is a protocol for a randomized controlled trial (RCT) that aims to assess the efficacy and safety of moxibustion, and to determine whether the optimal time of treatment for PD is preventively or after menstrual pain begins.

## Methods/Design

### Setting

This RCT will be conducted in a single center, with the assessor and statistician blinded to treatment allocation. A total of 222 patients diagnosed with PD in accordance with the Clinical Guidelines of Primary Dysmenorrhea by the Society of Obstetricians and Gynecologists of Canada will be enrolled in this trial [25]. The whole treatment process will be carried out in the Third Teaching Hospital of Chengdu University of Traditional Chinese Medicine, Chengdu, Sichuan, China.

### Patients

#### Recruitment strategies

There will be three strategies for PD patient recruitment. First, participants will be recruited from the outpatient and inpatient department of the Third Teaching Hospital of Chengdu University of TCM. Second, printed recruitment posters will be distributed in public clinics and nearby communities. Third, advertisements will be published in the campuses of Chengdu University of TCM, Sichuan University, Southwest University of Nationalities and Southwest Universities of Finance and Economics, and Sichuan Vocational and Technical College of Communications.

#### Inclusion criteria

Participants meeting the following criteria will be included:Aged from 18 to 30 years without history of delivery,Normal menstrual cycle (28 ± seven days) during the last three months,Diagnosed with PD according to the Primary Dysmenorrhea Consensus Guidelines [25],Diagnosed with the TCM pattern of stagnation of *Qi* and blood, or retention of cold-damp coagulation (see Table 1) [26],

**Table 1 Tab1:** **Traditional Chinese medicine pattern differentiation protocol for women with primary dysmenorrhea**

**Diagnostic patterns**	**Items**
**Diagnostic pattern 1**	
Stagnation of *Qi* and blood	Pain: distended, stabbing abdominal pain before or during the period aggravated by pressure.
	Menstruation: dark purplish in color, clotty and hesitant or scanty in flow, pain relieved after clots discharged.
	Accompanying symptoms: distending in breasts, mood swings.
	Tongue: purplish.
	Pulse: wiry.
**Diagnostic pattern 2**	Pain: distended, stabbing abdominal pain before or during the period, favorably to warmth, lower back pain.
Retention of cold-damp coagulation	
	Menstruation: dark purplish in color, clotty and hesitant in flow, pain relieved after clots discharged.
	Accompanying symptoms: distending in breasts, mood swings, and aversion to cold.
	Tongue: pale and white greasy tongue coating.
	Pulse: deep and slow.Menstrual pain score of over 40 mm on the Visual Analogue Scale (VAS),Agree to keep a dysmenorrhea diary during the study period, andAgree with all procedures in this trial by signing a written informed consent form.

#### Exclusion criteria

Participants meeting one or more of the following criteria will be excluded:Secondary dysmenorrhea caused by endometriosis, uterine myoma, endometrial polyps, pelvic inflammatory disease, or other gynecological problems confirmed by a gynecological abdominal ultrasound B examination;Serious contraindications (for example, a life-threatening condition or progressive central nervous disorder);Any other condition that the investigator judges as likely to make the patient unable to complete, comply, or unsuitable for the study;Uncontrolled diagnosed psychiatric disorders;Intent to have a baby during any period of the trial;Having taken antidepressants, anti-serotonin, barbiturates, or psychotropic drugs in the previous two weeks; orCurrently receiving or having received any other treatment for PD in the previous three months.

#### Sample size

A previous study found that the mean on the Cox Menstrual Symptom Scale (CMSS) of PD patients after moxibustion was 1.62 [24]. The average CMSS values of subjects in the proposed study, with the square of standard deviation, are expected to be 1.7, 1.9, and 2.5 for patients treated with moxibustion before menstruation, those treated at the time of menstrual onset, and the waiting list group, respectively. In this case, the three groups are set with the ratio of 1:1:1 as the statistical power is 0.90 and the significance level is 0.05. The sample size was estimated by One Way ANOVA Power Analysis (11th edition, NCSS, LLC, Utah, United States) in NCSS-PASS (11th edition, NCSS, LLC, Utah, United States). After the estimation, the effect size is 0.2266 with 64 patients in each group and 192 patients in total. Therefore, there should ideally be 222 patients in total, with each group containing no less than 74 patients, estimating a dropout rate is 15%.

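### The sample size calculation claims 90% power, but its own effect size and group size give 80%, and the dropout allowance falls slightly short of 192 completers

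*Protocol article*

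**What the plan says.** All the figures are in the Sample size section of the protocol article.

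- The targets are given as "the statistical power is 0.90 and the significance level is 0.05".
- The mean Cox Menstrual Symptom Scale (CMSS) values for treatment before menstruation, treatment at onset and waiting list "are expected to be 1.7, 1.9, and 2.5". The sentence refers to a variance ("with the square of standard deviation") but prints no value for it.
- On method: "The sample size was estimated by One Way ANOVA Power Analysis", run in PASS 11 with equal allocation.
- The result is that "the effect size is 0.2266 with 64 patients in each group and 192 patients in total".
- The total is then raised to 222, "with each group containing no less than 74 patients, estimating a dropout rate is 15" per cent.

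The total of 222 is repeated in the Abstract, under Setting and in the Figure 1 legend. The Sample size section is the only justification given for it.

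**The concern.** For a one-way ANOVA with equal groups, the number of groups, effect size, group size and alpha together fix the power. The section states all four and also states the power, so the claim can be checked without any outside figure. An effect size near 0.23 with 64 per group looked too small for 90% power. The step from 64 to 74 also looked like multiplication by 1.15, which does not leave 64 after a 15% loss.

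If the power is overstated, a null or borderline result on the primary outcome would be read as if the design had a 10% chance of missing the assumed effect, when its own calculation gives about 20%.

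**Working it through.** **Inputs (all from the Sample size section).** Groups k = 3, allocation 1:1:1; means 1.7, 1.9, 2.5; effect size f = 0.2266; n = 64 per group, N = 192; alpha = 0.05; stated power 0.90; dropout 15%; inflated size 74 per group, 222 in total.

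**Step 1: reproduce the effect size.** The grand mean is (1.7 + 1.9 + 2.5)/3 = 2.0333. The SD of the means (divisor k) is

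√{[(1.7 − 2.0333)² + (1.9 − 2.0333)² + (2.5 − 2.0333)²]/3} = 0.3399.

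f = SD of means / within-group SD, so the implied within-group SD is 0.3399/0.2266 = 1.50. With SD exactly 1.5, f = 0.2266 to four decimals. The effect size therefore agrees with the printed means and an SD of 1.5. That SD is inferred. The power check below does not use it, because f is printed.

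**Step 2: power at the stated size.** Under the alternative, the F statistic is noncentral F with k − 1 = 2 and N − k = 189 degrees of freedom and noncentrality

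λ = N f² = 192 × 0.2266² = 192 × 0.05135 = 9.86.

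Power is the probability that this variable exceeds the central F critical value at alpha 0.05.

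| n per group | Power |
|---|---|
| 62.9 (74 less 15%) | 0.796 |
| 63 | 0.796 |
| 64 | **0.803** |
| 74 | 0.861 |
| 83 | 0.899 |
| 84 | 0.903 |

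So 64 is the smallest n for 80% power and 84 is the smallest for 90% (3 × 84 = 252). With 15% loss, 84/0.85 = 98.8, which rounds up to 99 per group (297).

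**Step 3: could another reading give 0.90 at n = 64?**

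- Alpha 0.10: power 0.879 at 64 per group; 69 per group would be needed for 0.90.
- Effect size defined with divisor k − 1: λ falls to 64 × 2 × 0.05135 = 6.57, so power would be lower still.
- A different SD: 0.90 at 64 per group needs f of about 0.259, that is SD 0.3399/0.259 = 1.31, which contradicts the printed 0.2266.
- A pairwise comparison at SD 1.5 for the largest difference (2.5 − 1.7 = 0.8): two-sided power 0.855 at 64 per group. Only a one-sided version exceeds 0.90 (0.915), and that is not the stated method. A two-sided comparison reaches 0.90 at 74 per group, but only with no dropout and only for that one pair. The text ties 0.90 to the ANOVA and to 64.

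**Step 4: dropout.** 64 × 1.15 = 73.6, which rounds up to the plan's 74. To keep 64 after 15% loss, the size is 64/0.85 = 75.3, or 76 per group (228). Inflating the total instead gives 192/0.85 = 225.9, or 226. With 222 randomised, 222 × 0.85 = 188.7 remain (62.9 per group). The loss that 74 per group can bear while leaving 64 is 1 − 64/74 = 13.5%.

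**The case against.** The strongest reply is that the section shows only that power, group size and effect size disagree, not which one is wrong. The target may really have been 0.90, with the error in n or in the SD. This stands in part. The exact match of 64 to the 80% requirement, and of f to the printed means with a round SD of 1.5, makes a run at 0.80 the likeliest explanation, but only the sponsor's PASS output can settle it. Whatever the origin, the power at the printed f and n is 0.803.

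Second, the Analysis section plans a repeated-measures ANOVA over cycles, whose power may differ from that of a one-way ANOVA. True, so the 20% is the type II error of the stated calculation and not a known property of the final analysis. But the 0.90 is attributed to the one-way ANOVA, and no between-cycle correlation is given to support another figure.

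Third, the dropout slip is small: about three completers and less than one point of power. The full analysis set also uses multiple imputation, so a 15% loss does not simply remove patients from it. This stands; the slip would not deserve a separate point. It does bear on the per-protocol set, which the Analysis section names for evaluating the curative effect.

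Fourth, the SD of 1.5 is an inference. That is correct, and the sponsor should confirm it.

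**Conclusion.** The concern holds. Under the plan's own method and printed inputs, power at 64 per group is 0.80, not 0.90, a gap of about ten percentage points. The claimed power would need 84 per group, and 74 per group without any loss gives 0.861. The dropout arithmetic is also wrong, but it matters little: 188.7 expected completers against 192, and power 0.796.

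The power result rests only on the printed effect size, group size, alpha and method. It concerns the overall three-group F test. It does not establish the power of the planned repeated-measures analysis, which cannot be worked out from the article.

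**What to change.** In the Sample size section:

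1. Check the figures against the original PASS output and restate the power as about 0.80 for effect size 0.2266 and 64 per group.
2. Print the within-group SD that was used. The means and effect size imply 1.5; the sponsor should confirm it.
3. Replace the dropout sentence with one saying that 74 per group retains 64 at up to 13.5% loss, and that a 15% loss leaves about 63 per group with power of about 0.80.
4. If 0.90 is to be claimed at 222 patients, support it with a new calculation for the planned repeated-measures analysis, stating the assumed between-cycle correlation. That calculation should not take credit for baseline CMSS adjustment unless baseline CMSS is collected; Table 2 marks CMSS only in the treatment and follow-up cycles.

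Items 1 to 3 are changes of wording. Their cost is a less favourable stated power. They need no extra patients and no change to procedures, provided the sponsor accepts about 0.80. Item 4 costs one further calculation.

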### Ethics

This study protocol was reviewed and approved by the Institutional Review Board of the Teaching Hospital of Chengdu University of Traditional Chinese Medicine in February 2014 (approval number: 2013KL-034). The present study was financially supported by the National Natural Science Foundation of China and the trial was registered in Chinese Clinical Trials Registry with the identifier number ChiCTR-TRC-14004627. Prior to undertaking any study-related procedures, all participants will provide written informed consent.

### Procedure

An independent assessor will initially assess each potential participant according to the inclusion and exclusion criteria. After completing a screening test, participants will enter a baseline period of three months (three menstrual cycles) without moxibustion treatment, during which they will be asked to record menstrual pain and use of acute medication in a dysmenorrhea diary.

### Randomization

After participants have completed a baseline evaluation, eligible subjects will be randomly classified into three groups: treatment group A (treated before menstruation), treatment group B (treated as the onset of menstruation), and control group C (waiting list group). A computer-generated, blocked random allocation sequence will be generated with SAS software (Version 9.1, SAS Institute Inc., NC, United States). Another research coordinator who is not involved with data collection will provide the random number and group assignment immediately to the independent assessor in opaque, sealed envelopes. This procedure guarantees that randomization concealment is adequate, and not influenced by the acupuncturists or participants. Random allocation will be performed after the first visit to participants who provide informed consent and meet the inclusion criteria. If a participant is eligible to be included in the study, the researcher will open the corresponding envelope in front of the participant. The envelopes will be opened only after the enrolled participants have completed all baseline assessments.

Figure 1 summarizes the design of the study and Table 2 outlines the measures used in the trial. The duration of the study for every participant will be nine menstrual cycles, including three menstrual cycles in the baseline, treatment, and follow-up periods, respectively.

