**Figure 1 Fig1:**
[figure not shown]
**Flow chart of the trial.** Participants with a diagnosis of primary dysmenorrhea will be recruited at the Third Teaching Hospital of Chengdu University of Traditional Chinese Medicine. All participants should endure a baseline period of three menstrual cycles and inappropriate participants will be excluded. A total of 222 participants will be randomized to three groups: treatment group A (treated before the menstruation), treatment group B (treated at the onset of menstruation), or control group C (waiting list group) in a 1:1:1 ratio. The trial period will consist of three baseline menstrual cycles, three menstrual cycles of treatment, and three menstrual cycles in the follow-up period, and the outcome will be measured at every visit.

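### The role that screens eligibility is also given the assignments from a blocked list, so the stated guarantee of allocation concealment is too strong

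*Protocol article*

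**What the plan says.** The protocol article, Randomization, describes the list thus: "A computer-generated, blocked random allocation sequence will be generated with SAS software". A coordinator not involved in data collection "will provide the random number and group assignment immediately to the independent assessor in opaque, sealed envelopes". For an eligible woman, "the researcher will open the corresponding envelope in front of the participant", and this happens only once the baseline assessments are complete. The section concludes: "This procedure guarantees that randomization concealment is adequate, and not influenced by the acupuncturists or participants".

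The Procedure section uses the same role title for entry: "An independent assessor will initially assess each potential participant according to the inclusion and exclusion criteria".

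Three other statements bear on the point:
- Setting: the trial has one centre, and the assessor and statistician are blinded to allocation.
- Blinding: clinician and patient cannot be blinded. Therapist, assessors of therapeutic effect, data manager and statistician are kept separate. The person who screens eligibility is not in that list.
- Entry involves judgement. One exclusion criterion reads "Any other condition that the investigator judges as likely to make the patient unable to complete, comply, or unsuitable for the study", and the legend to Figure 1 adds "All participants should endure a baseline period of three menstrual cycles and inappropriate participants will be excluded".

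**The concern.** This concerns selection at entry. An opaque, sealed envelope stops someone reading the next assignment. It does not stop someone inferring it from earlier assignments in the same block. Inference needs a record of past assignments, and acting on it needs influence over who enters next. On the plain wording, one role title has both.

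If a recruiter could tell that the next place was, or was not, the waiting list, a woman might be deferred or excluded according to her severity or enthusiasm. With a waiting-list comparator and self-rated outcomes, that could bias moxibustion against waiting list, and also group A against group B. Table 2 shows the primary scale (CMSS) only from the first treatment cycle onward, so an imbalance on that scale before treatment would not be seen directly.

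There is also a tension with Setting: an assessor who is handed the group assignment is hard to describe as blinded to it, if the same person is meant.

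**Working it through.** **Step 1: the text.** Procedure gives eligibility screening to an independent assessor. Randomization gives the group assignment to the independent assessor. Setting says the assessor is blinded to allocation. Nothing in the article states that these are different people. Randomization names acupuncturists and participants as parties who cannot influence allocation; it does not name the assessor.

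**Step 2: how much earlier assignments reveal.** The article gives no block size and no figure on predictability, so there is no stated result to reproduce. Block size is therefore an assumption, shown over a range.

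Inputs: three arms at 1:1:1 and 222 participants (Abstract, Sample size). Assumptions: one sequence, a fixed block of b = 3k, and an observer who knows b and every earlier assignment. Guessing at random is right 33.3% of the time.

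- *Assignment certain.* A card is certain when all 2k cards of the other two arms in its block have gone before it. Among those 2k + 1 cards each order is equally likely, so the probability is 1/(2k + 1).
- *Treated versus waiting list certain.* A waiting-list card (one third of cards) needs all 2k treated cards before it; a treated card (two thirds) needs all k waiting-list cards before it. The share is (1/3) × 1/(2k + 1) + (2/3) × 1/(k + 1). For k = 2: 1/15 + 2/9 = 0.289.
- *Best guess correct.* For b = 3: (1/3 + 1/2 + 1)/3 = 0.611. Larger blocks by exact enumeration.

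| Fixed block | k | Certain | Of 222 | Treated vs waiting list certain | Best guess correct |
|---|---|---|---|---|---|
| 3 | 1 | 33.3% | 74 | 44.4% | 61.1% |
| 6 | 2 | 20.0% | about 44 | 28.9% | 56.1% |
| 9 | 3 | 14.3% | about 32 | 21.4% | 53.2% |
| 12 | 4 | 11.1% | about 25 | 17.0% | 51.2% |

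**Step 3: varying blocks.** Simulation of an observer who knows the possible sizes but not the current one:

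| Sizes mixed at random | Certain | Best guess correct |
|---|---|---|
| 3, 6 | 8.9% | 57.7% |
| 3, 6, 9 | 3.9% | 55.4% |
| 6, 9, 12 | 2.5% | 53.0% |

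Varying the blocks removes most of the certainty. It hardly moves the best guess: 55.4% for the 3, 6, 9 mix against 56.1% for a fixed 6. Keeping past assignments away from whoever decides entry therefore matters under every scheme examined.

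**The case against.** The strongest reply is that an article condenses a full protocol. Block size, variation and stratification are commonly left to that document, which may already use varying blocks. The described safeguards are real: opaque sealed envelopes, a coordinator outside data collection, and opening only after baseline. The article also uses three titles: the independent assessor screens, the investigator applies the discretionary exclusion, and the researcher opens the envelope. It does not say that they are one person, or that the assessor sees the contents of every envelope. All of this stands, and it limits the point to the stated routing and the stated guarantee.

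Four stronger readings are tempting but not supported:
- *That the block must be 3 or 6.* A reader might infer this from "there should ideally be 222 patients in total, with each group containing no less than 74 patients", since 3 × 74 = 222 and neither 9 nor 12 divides 222. But this is an ideal recruitment target after a dropout allowance. A list can stop mid-block, and varying blocks can also sum to 222.
- *That the list is plain and unstratified.* That is inferred from silence.
- *That recruiting staff see the full history of assignments.* That requires merging roles which the article names separately.
- *That the analysis could not repair any damage.* VAS, RSS and the diary are collected before treatment and could show a severity imbalance. The covariates in the Analysis section are introduced as examples, not as a closed list. What is true is only that CMSS itself has no pre-treatment value in Table 2.

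The objection does not rescue the guarantee. The safeguards prevent reading the current card, not inferring it from earlier ones, and the wording does send assignments to the role that screens.

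**Conclusion.** The point holds in a limited form. As written, the article passes assignments from a blocked list to the role title that screens eligibility, in an open single-centre trial whose assessor is said to be blinded. Concealment is therefore not guaranteed by the procedure described, and the role of the assessor needs to be reconciled between Setting, Procedure and Randomization.

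The size of the risk cannot be fixed from the article. Certain assignments range from one third (fixed block of 3, known to the observer) to about 2.5% (withheld mix of 6, 9 and 12). Every figure assumes that the observer sees all earlier assignments, and the fixed-block figures also assume a known block size. The article establishes neither. It does not show that selection has occurred or that assignments can often be worked out. The case for change rests on the overlap of roles, which is cheap to remove, and not on any one predictability figure.

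**What to change.** Amend the Randomization section as follows:

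1. Do not pass assignments to anyone who screens eligibility or rates outcomes. State who receives them and who opens the envelope, and confirm that this person takes no part in entry decisions.
2. Have the existing coordinator hold the list or envelopes and release one assignment at a time to the unblinded treating side. Release it only after final eligibility, including the check after the baseline cycles, is signed off and the enrolment number is irrevocably logged.
3. Keep the block scheme undisclosed to recruiting staff. If the unprinted list uses a fixed small block, vary the block size for participants not yet randomised.
4. Replace the sentence that guarantees concealment with a description of these steps, and align Setting and Procedure with it.

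The cost is a short amendment and slightly more logistics, with the coordinator already in place. If the list has to change, the allocation program is re-run once for the remaining participants, and group sizes may end a few away from 74. Trial status says that recruitment is still open, and allocation follows three baseline cycles, so later participants can still benefit.
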